### Plans to give access to the full protocol, participant-level data and statistical code {31c}

We will create a data archive that will contain raw study data (no identifiers). These data will be available to other investigators upon formal request to the principal investigator, following the publication of the primary analyses of the project, and after the data have been appropriately checked, cleaned, and de-identified. The archive will reside on a server for which appropriate firewalls and other forms of data protection will be installed for maximum security. Prospective users will complete an application for use of the data, which will include queries about the users’ project hypotheses and proposed analyses. All NIH regulations and restrictions as well as HIPAA Security Rules regarding personal health information will be observed.

## Oversight and monitoring

### Composition of the coordinating center and trial steering committee {5d}

*NYU Grossman School of Medicine*: this will be the primary site for general management and overview of the study, as well as statistical analysis, and formulation of presentations and manuscripts. *Mahidol University*: The Ratchasuda College and Faculty of Information and Communication Technology (ICT) will contribute to this research project by mapping areas of interest and conducting the field trials of VIS^4^ION with visually impaired students at Ratchasuda College, Mahidol University, Salaya campus and within the extended environment in urban Bangkok, as well as the investigations focused on human and system adoption in different contexts, assessing the impact on quality of life in a low-resource setting and gauging future scalability. ICT members will integrate required hardware and software for study experimentation purposes.

*NYU Tandon*: School of Engineering: a primary site for neural network data analysis and developing the wearable device.

### Composition of the data monitoring committee, its role and reporting structure {21a}

Data Monitoring Committee (DMC): is the primary body for study-related decision-making and is responsible for its successful completion, including target enrollment, subject retention, and protocol adherence. The Committee comprises all study investigators. PI is the chair of the Committee. On issues requiring a vote, one vote per member will be allowed. The ultimate authority over the conduct of the research will reside with the study PI. The DMC meets monthly or more frequently, as required.

The primary responsibilities of the DMC include:+ Approving all study-related documents, including:- Study protocol,- Informed consent form, and- Data and safety monitoring plan (DSMP),+ Reviewing and subsequently voting on top protocol and operational issues;+ Receiving and reviewing all reports from team members, in order to provide recommendations and guidance regarding potential study issues;+ Assisting in the development of corrective action plans if enrollment targets are not being met or noncompliance with the protocol has been noted; and+ Overseeing the dissemination and publication of study results.

### Adverse event reporting and harms {22}

Overall, the risk to participants is minimal: the likelihood of physical/psychological harm does not exceed what would be encountered in ordinary life. Subjects will be learning how to use a new assistive device and during this learning period, the subjects may be at a slightly greater risk of injury. Once the subject is accustomed to the device, the risk of injury would not exceed that in ordinary life.

The proposed psychophysical procedures pose no risk (the most likely negative consequence being boredom or fatigue). Subjects will be encouraged to rest should they feel any fatigue.

This risk is minimized through careful handling and storage of data and training of staff members. Subjects will be told to contact the PI if they experience a research-related injury. Should new information become available during the research that may affect a participant’s willingness to participate, all participants will be notified. Additionally, should any adverse effects of the procedures be demonstrated in the future, every attempt to notify participants will be made.

All adverse events will be immediately reported to the Ethics Committee.

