Each FGD session will last roughly 60 min and include participants’ perceptions and experiences while navigating the VIS^4^ION system. The FGDs will be guided by pre-determined questions related to general perceptions of the VIS^4^ION system, as well as thoughts on the facilitators and barriers of the intervention. The FGD sessions will be audio-recorded verbatim and later transcribed and translated into English by the research team. During the sessions, the research team member will also take field notes.

#### Aim 4

A cohort of 20 (new) participants will be recruited to assess extended-use benefits over one month. We will create two groups for the randomized crossover design. Each participant will be randomized to either sequence A (10 participants) or sequence B (10 participants). During the first 15 days, group A will go through an active phase and then a passive phase for the next 15 days. Reciprocally, group B will go through a passive phase for the first 15 days and then an active phase for the second half of the month. During the passive phase, the wearable will be maintained in a monitoring mode and simply acquire data, providing no assistance/feedback on location and orientation. During the active phase, the wearable will have an activated assistive mode, i.e., the wearable will acquire data and simultaneously provide assistance/audio feedback. We will evaluate the effectiveness of the wearable for increasing navigation and quality of life. We hypothesize that the VIS^4^ION wearable will improve navigation and quality of life in individuals with visual disabilities.

During the active phase, subjects will complete their daily activities while wearing VIS^4^ION and using the mapping and localization microservice to facilitate wayfinding. Throughout the study we will monitor navigation performance through the same metrics as delineated in Aim 2 [week 2 compared to week 4], as well as to monitor for any falls that may occur (IMU-based alerting); we will also subjectively assess visual function through the 25-Item National Eye Institute Visual Function Questionnaire (VFQ25) [29], physical function and mobility, through the International Physical Activity Questionnaire (IPAQ) [30, 31], and QoL, through the World Health Organization QoL Brief (WHO-QoL-BREF) [32, 33]. The subjective assessments will be performed on day 0 (day of device delivery and initiation) and on the final day of the trial (day 31).

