### Strategies to improve adherence to interventions {11c}

Since subjects will be in the study for a sustained period (for each respective phase), given scheduling requirements, the dedicated research coordinator will clearly communicate expectations to help overcome any potential difficulties. We will make our best attempts to obtain 3 different contact options to ensure that we are able to communicate with the subjects on an ongoing basis.

We will ensure that access to study facilities is aided by route mapping/transportation planning, ensuring the retention of patients given inconvenient geographic logistics from the research site-to-domicile.

Training of clinical and study staff will ensure streamlined communication and avoid miscommunication. A research coordinator at Ratschasuda College will coordinate study assessments while the investigative team will maintain open channels of communication between relevant study facilities for any query at any time point. A clear division of labor and frequent communication will ensure that we retain subjects in the study.

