## Assignment of interventions: blinding

### Who will be blinded {17a}

The study will be single-blind. Participants and a designated team member will not be blinded to the intervention. However, study team members who introduce and explain the system to each participant will be blinded and will not know if the participants are part of groups A or B. A blinded analyst will perform statistical analysis.

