## Data collection and management

### Plans for assessment and collection of outcomes {18a}

After each session, the collected data will be audited by a designated study team member to ensure the quality of collected data and troubleshoot any unforeseen technical issues. In addition, we will use IMU-based altering to monitor for any falls. For our subjective assessments, we will use the 25-Item National Eye Institute Visual Function Questionnaire (VFQ25) [38], the most frequently used measure of patient-reported, vision-related functioning. The NEI VFQ-25 was developed based on qualitative research with patients to measure the range of vision-related functioning experienced by persons with VI. We will use the International Physical Activity Questionnaire (IPAQ) to assess physical activity. It is a widely used self-reported questionnaire with excellent test reliability for overall score (ICC = 0.81) and physical activity (ICC = 0.84–1.00) [30]. We will administer the World Health Organization QoL Brief (WHO-QoL-BREF) to assess and compare the quality of life. WHO-QoL-BREF is 26 items, self-reported questionnaires that address 4 domains of quality of life, including physical health, psychological health, social relationships, and environments. This test was developed collaboratively and field-tested across several cultural contexts, therefore it is highly recommended to study outcomes and/or measure the quality of life [32, 33].

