### Confidentiality {27}

Confidentiality of research records will be strictly maintained. All computerized data files will be de-identified and will not contain any information that could be used to identify individual subjects. Rather, data files will be assigned a unique alphanumeric identifier. The code key connecting the data with the subjects’ names will be kept in a separate, secure location. Data will be backed up to a secure research drive. Only the PI and coinvestigators will be able to access the data.

The results of these experiments may be published (book or journal) or used for teaching purposes. The identities of participants and participants’ family members will not be revealed in any publication or teaching material without specific permission. After publication, the data may be removed from the PI’s computers and file servers.

The PI will promptly report all adverse reactions to the IRB. An annual report on data and safety monitoring will be submitted to the IRB. This report will detail any adverse events.

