**Fig. 4 Fig4:**
[figure not shown]
Correlations between ground truth positions and those computed from Pos-Net and Loc-Net (left) and corresponding 2D errors (right)

We have collected a small sample of preliminary data (Fig. 4) to demonstrate the feasibility of these analyses, and that they are capable of demonstrating improvement (green; Loc-Net) relative to our baseline (blue; prior art) methods. There is a clear, qualitative improvement in the green plots, both in precision (left, improved correlation) and accuracy (right, error scatter). Our ability to discriminate between methods will only improve with the larger dataset proposed for this aim.

#### Aim 2

We will use the trained network to predict the real-time pose of a BLV user and create a mobility home range for each participant during both the passive and active phases of this initial pilot. We anticipate that route planning will improve through more efficient wayfinding in the active phase, when users have a more comprehensive understanding of the local environment (spatial cognition). We will extract paths between pre-selected pairs of locations during the active and passive phases (e.g., residence to classroom building) traversed in the pre (first 5 days) and post (last 5 days) periods to evaluate our predictions, measuring:Average changes and variability in path length (i.e., percent change in path length [difference test based on binomial distribution] and path variance [F-test of variances])Average changes in normalized traversal time (i.e., percent change in time [difference test based on binomial)For destinations that denote social activities, estimate the difference in time spent on such activities pre to post [time difference based on Wilcoxon signed rank test].Pre vs. post fall rates using an exponential waiting-time model of time between falls [Poisson rate of falling]Total area covered on an hourly, daily, and weekly basis to assess a home range

#### Aim 3

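### The stated injury-reporting rule depends on the unblinded participant's own view of relatedness, so capture of injuries other than falls can be incomplete and can differ between active and passive mode

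*Protocol article*

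**What the plan says.** All references are to the protocol article.

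- **Intake of injuries.** Adverse event reporting and harms {22}: "Subjects will be told to contact the PI if they experience a research-related injury". The section closes by committing to immediate onward reporting of every adverse event to the Ethics Committee, with no condition on relatedness.
- **Onward reporting.** Confidentiality {27}: "The PI will promptly report all adverse reactions to the IRB".
- **Blinding.** Who will be blinded {17a}: "Participants and a designated team member will not be blinded to the intervention".
- **Falls.** Intervention description {11a}, Aim 4, plans navigation monitoring "as well as to monitor for any falls that may occur (IMU-based alerting"). Plans for assessment and collection of outcomes {18a} repeats this in general terms: "we will use IMU-based altering to monitor for any falls" (the printed word is evidently a slip for alerting). In passive mode "the wearable will be maintained in a monitoring mode and simply acquire data", so recording is not confined to active mode. Fall rates are a listed outcome in Aims 2 and 4; the Aim 2 analysis is "Pre vs. post fall rates using an exponential waiting-time model of time between falls".
- **Collisions.** Interim analyses {21b} describes weekly data quality checks of the collision rate against baseline, feeding a Bayesian assessment of early halting. It does not say how a collision is detected or recorded.
- **IMU before Aim 5.** Statistical methods {20a}, Aim 5, says that GPS and IMU signals for detecting falls and collisions are an addition at that stage and had not been in use before.

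**The concern.** The intake rule in {22} applies two filters before the trial learns of an injury: the participant must think it was caused by the research, and must then make contact. Both are applied by someone who knows the mode. A head strike while cues are sounding may seem to be the device's doing; the same event while the bag only records may seem part of ordinary life. If so, the event is less likely to be reported in passive mode.

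Two things depend on capture. First, {22} states that injury risk will not exceed the everyday level once the user is accustomed to the device. Checking that needs reasonably complete ascertainment that does not depend on mode. Second, the early-halting assessment in {21b} rests on a collision count whose source is not given. If that count leans on participants' calls, the halting assessment inherits the same filters.

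**Working it through.** **Step 1: which injuries have a source other than the participant's call?**

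| Event | Stated source, Aims 2 and 4 | Aim 5 |
|---|---|---|
| Fall | IMU alerting ({11a} Aim 4; {18a} generally), in both modes; contradicted by the Aim 5 text in {20a} | GPS and IMU |
| Collision | Weekly check in {21b}, source of the count not named | GPS and IMU |
| Any other injury | None beyond the participant's call | None beyond the participant's call |

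In Aim 4 the dated subjective assessments are day 0 and day 31. None is stated at the change of mode after day 15, so no dated assessment separates recalled injuries by mode.

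**Step 2: does the intake rule match the onward commitment?** The commitment covers every adverse event; the rule invites only those the participant attributes to the research. An injury thought unrelated, and not a fall or collision detected some other way, has no stated path to the investigator and so cannot be passed on.

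**Step 3: what could this do to the counts?** The documents give no injury rate, reporting probability or sensor-detected share, so there is no figure to reproduce. All inputs here are assumptions. Let true injury rates and time at risk be equal in the two modes, *f* the share of injuries detected by sensor, and *pA* and *pP* the probabilities that the remainder are reported in active and passive mode.

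- Captured share in active mode: *cA* = *f* + (1 − *f*)·*pA*; in passive mode: *cP* = *f* + (1 − *f*)·*pP*
- Apparent active:passive ratio = *cA* / *cP*
- Overall capture = (*cA* + *cP*)/2

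| *f* | *pA* | *pP* | Apparent ratio | Overall capture |
|---|---|---|---|---|
| 0 | 0.9 | 0.6 | 0.90/0.60 = 1.50 | 75% |
| 0 | 0.6 | 0.3 | 0.60/0.30 = 2.00 | 45% |
| 0 | 0.5 | 0.5 | 0.50/0.50 = 1.00 | 50% |
| 0.5 | 0.9 | 0.6 | 0.95/0.80 = 1.19 | 87.5% |
| 0.5 | 0.6 | 0.3 | 0.80/0.65 = 1.23 | 72.5% |
| 1 | any | any | 1.00 | 100% |

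Distortion between modes needs unequal reporting and affects only injuries the sensors miss. Equal but incomplete reporting lowers the total and leaves the ratio at 1. Swapping the probabilities in the first row gives 0.60/0.90 = 0.67, so the direction is not fixed either.

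**The case against.** A reader might infer that injuries reach the trial only through the participant's call, and that harms are therefore under-counted and biased. The documents do not support that. IMU fall alerting is stated, the device records in passive mode too, fall rates are a planned outcome, and collisions are checked weekly. Falls and collisions are plausibly the main injury mechanisms here. The sentence in {22} is also an instruction to participants and does not claim to be the sole method of ascertainment.

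Three further points count against a strong reading. The section on the data monitoring committee {21a} names a data and safety monitoring plan that is not shown, and an article normally leaves adverse event forms to such a document; the absence of scheduled questions is not in itself a fault. No active-versus-passive comparison of self-reported injuries is planned. And the reporting probabilities above are assumed.

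These points remove the word *only* and any claim of demonstrated bias. They do not remove the mismatch inside {22}, which lies between two things the article states. Nor do they supply a source for the collision count in {21b}. The fall safeguard is itself in doubt while the Aim 5 text in {20a} stands against {11a} and {18a}. The Aim 5 remark may have been meant for localisation alone, but as printed it names falls and collisions.

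**Conclusion.** The point holds in a limited form. The stated intake rule filters injuries by an unblinded participant's view of relatedness and cannot by itself meet the commitment to report every adverse event. For falls, the stated IMU source largely answers the concern, provided it operates in Aims 2 and 4, on which the article contradicts itself. For collisions before Aim 5 the source is not stated, and for other injuries there is no second source. Capture of non-fall injuries can therefore be incomplete and can differ by mode.

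Neither size nor direction can be derived. Ratios of 1.5 or 2.0 are illustrations under assumed reporting probabilities and no sensor detection; with half of injuries sensor-detected, the same assumptions give about 1.2, and with equal reporting 1.0. The case for change rests on the internal mismatch and the low cost of repair, not on these figures.

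**What to change.** 1. In {22}, remove the participant's judgement of relatedness from intake. Keep the instruction to call the PI as an additional route.
2. In Aims 2 and 4, have the coordinator ask a short, cause-neutral question: any injury, fall or collision since the last contact. Ask it on the same study days, counted from the start of each mode, and at the change of mode. The investigator judges causality afterwards.
3. In Aim 5, ask the same question at fixed contacts. No mode comparison is described there, so none is needed.
4. Name these answers in {21b} as a source for the weekly collision count.
5. Reconcile the Aim 5 text in {20a} with {11a} and {18a} on whether IMU fall detection operates before Aim 5.

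**Cost.** One paragraph and a short form. A coordinator is already planned, and {11c} already provides for contact options "to ensure that we are able to communicate with the subjects on an ongoing basis". The downside is a few minutes per contact and a higher recorded event count, which should be expected when the results are read.

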### Frequency and plans for auditing trial conduct {23}

We have bi-weekly meetings to assess research completion as set in the research outline and weekly data quality monitoring. PI and Co-Is receive monthly reports from team members during recruitment and experiment to monitor adherence to protocol. We will assess the dissemination of activities by tracking peer-reviewed publications, presentations in national and international conferences, and poster presentations.

We submit NIH’s annual progress report. Also, the Independent Monitoring Committee (IMC) audits the trial. The IMC will comprise three members, a PhD-level biostatistician and two experts in the field. However, they are not otherwise associated with this research project and work independently of the PI. The IMC will meet annually and recommend to the PI whether the study should continue as planned, continue with modifications, or be stopped.

### Plans for communicating important protocol amendments to relevant parties (e.g., trial participants, ethical committees) {25}

The reportable events noted above will be reported to the IRB using the form: “Reportable Event Form” or as a written report of the event (including a description of the event with information regarding its fulfillment of the above criteria, follow-up/resolution and need for revision to consent form and/or other study documentation). Copies of each report and documentation of IRB notification and receipt will be kept in the Clinical Investigator’s study file.

### Dissemination plans {31a}

The final data will be made available in formats that are considered an industry standard for our field of research. The data elements will enable comparisons between research studies and allow for reproducibility, facilitating larger research endeavors. All data will be de-identified; anonymized forms will be disseminated. Publication of the data sets relevant to this study proposal will follow the publication of research findings from the study-specific projects. Data will also be used for national meetings and symposia.

The results of these experiments may be published (book or journal) or used for teaching purposes. The identities of participants and participants’ family members will not be revealed in any publication or teaching material without specific permission.

## Discussion

Perhaps the greatest difficulties and dangers faced by the BLV involve those encountered during locomotion and navigation; ameliorating these difficulties would significantly improve the lives of these individuals. Although electronic aids for navigation seem like an attractive solution, there are several barriers to their use, chief among them being their dependence on either environmental (sensor-based) infrastructure or WiFi/cellular “connectivity” infrastructure or both. Here we propose a navigation solution that operates independently of both environmental and Wi-F/cellular infrastructure, as well as tests of both the performance of the system and the function/health benefits gained from use. Furthermore, this system was uniquely created to excel in low-resource settings with poor telecommunications. Thus, it is uniquely poised to deploy in LMICs. In the current proposal, we intend to deploy the system and perform staged evaluations within environments of progressive difficulty; we also intend to acquire patient-centered feedback from interviews and questionnaires.

Future studies are needed to promote the expansion of software-based mapping and localization microservices deployed through advanced wearables. More broadly, advanced wearables may serve as a foundation on which to build modular wayfinding tools turned into best practices for improved health and well-being. While our current proposal helps to build upon rigorous prior literature and expand our knowledge base regarding assistive technology and implementation science in low-resource settings for the BLV, we intend to expand the disabilities addressed and experiment with both cognitive and social disabilities, including mild cognitive loss, dementia, and autism. As the study of BLV ecology (mobility phenotyping [42]) is a robust and logical next step in the science of wayfinding, we intend to further diversify the disabilities characterized, geographic regions examined, and cultural contexts incorporated.

